#### Adverse events and monitoring safety

All unexpected adverse events related to pricking blood at ExHN 9 and acupuncture treatment at LI 20 will be reported to the investigator or acupuncture practitioner by participants and written on the individual case report form by the investigator. Safety will be assessed using clinical laboratory tests, vital sign measurements, and adverse events. Clinical laboratory tests, including AST/ALT, BUN/creatinine, red blood cell (RBC) count, white blood cell (WBC) count, hemoglobin, hematocrit, mean cell volume (MCV), mean cell hemoglobin (MCH), mean cell hemoglobin concentration (MCHC), number of platelets, and number of differentiated cells will be determined at weeks 0 (baseline) and 3 (end of the trial). Vital signs of each participant will be checked by monitoring adverse events (pain on the acne lesion or other sites, nausea/vomiting, fatigue, allergic reaction, and any adverse events related to acupuncture) after each visit.

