### Participants and eligibility

#### Inclusion criteria

Eligible for inclusion in this study will be patients ≥ 8 years of age with a diagnosis of NAR and at least a 3-month history of continuous nasal symptoms related to defined triggers (for example, changes in temperature and/or humidity, strong odors, and airborne irritants). Patients must have had a history of negative results in allergic tests (MAST test, serum IgE) and an eosinophil count within a normal range.

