#### Intervention

Three sessions will be used for both pricking the blood at ExHN 9 and acupuncture treatment at LI 20. The sessions will be administered over a period of 3 weeks (one session per week). Certified acupuncture practitioners who have a minimum of 3 years of clinical experience obtained after a 6-year oriental medical college course will perform the acupuncture treatment. The practitioners will take a one-day training course for this trial. This course will include the study protocol, methods for acupuncture treatment, and basic information on clinical research.

#### Pricking blood at ExHN 9

Three sessions of pricking blood at ExHN will be performed once per week for 3 weeks in patients assigned to the experimental group. Patients that will receive acupuncture treatment will be pricked on the intranasal membrane at bilateral ExHN 9, which is located at the junction between the mucosa of the alar cartilage of the nose and the nasal concha in the nostril. This point will be treated with 0.30 × 120 mm disposable acupuncture needles (Dongbang Co., Korea) according to 'WHO Standard Acupuncture Point Locations' in the Western Pacific Region [17].

#### Acupuncture treatment at LI 20

Three sessions of acupuncture treatment at LI 20 will be performed once per week for 3 weeks in patients assigned to the control group. Patients will receive acupuncture treatment at bilateral LI 20. For bilateral LI 20, needles will be inserted obliquely toward their ipsilateral nostrils to a depth of 0.3 cm. This point will be treated with 0.30 × 40 mm disposable acupuncture needles (Dongbang Co., Korea) according to 'WHO Standard Acupuncture Point Locations' in the Western Pacific Region [17]. Patients will remain in the supine position for 15 min during acupuncture treatment.

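### The two adverse event sentences disagree on scope, and the monitored list names an acne lesion but no nasal event, so local harms of intranasal pricking may be under-recorded

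*Protocol article*

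**What the plan says.** The section Adverse events and monitoring safety makes three statements about adverse events.

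- **Reporting rule.** "All unexpected adverse events related to pricking blood at ExHN 9 and acupuncture treatment at LI 20 will be reported" by participants to the investigator or the acupuncture practitioner, and then "written on the individual case report form by the investigator".
- **Safety measures.** "Safety will be assessed using clinical laboratory tests, vital sign measurements, and adverse events". Adverse events carry no qualifier here.
- **Monitoring at visits.** A sentence that begins with vital signs gives a list in brackets: "pain on the acne lesion or other sites, nausea/vomiting, fatigue, allergic reaction", "and any adverse events related to acupuncture) after each visit".

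Two other sections give the context. The Inclusion criteria admit "patients ≥ 8 years of age with a diagnosis of NAR". Under Intervention, patients in the experimental arm "will be pricked on the intranasal membrane at bilateral ExHN 9", once a week for three weeks.

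**The concern.** Expectedness and relatedness are judgements made about an event after it is known. Here they appear as conditions for entering it on the case report form. For a procedure intended to draw blood from the nasal mucosa, the most foreseeable harms are local, and a foreseeable harm is the kind that staff may class as expected and leave out. The monitored list could have guarded against this by naming local events. Instead it points to a site that does not exist in this trial and leaves nasal events to a catch-all.

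Safety is a stated assessment, children from age 8 are eligible, and the Discussion presents this as the first randomized trial of the procedure's efficacy in this condition. With 25 patients per arm, there is little safety information to lose. The arms also differ in site and type of procedure, so a filter on expectedness need not fall equally on both, even though its wording is the same for both.

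**Working it through.** **Step 1. Compare the two scopes.** The article states no safety figure to reproduce, so the check is mainly textual.

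| | Reporting rule | Monitoring sentence |
|---|---|---|
| Must be unexpected? | Yes | No |
| Must be related? | Yes | Not for the named items; yes for the catch-all |
| Stated to reach the case report form? | Yes | Not stated |
| Names a nasal event? | No | No |

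**Step 2. Trace typical events through both sentences.**

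- *Unexpected and related:* covered by the reporting rule.
- *Nasal pain after pricking:* fits the other-sites wording of the list. If classed as expected, it has no stated route to the case report form.
- *Nasal bleeding or local infection after pricking:* not named. The Discussion describes the pricking as a modified form of acupuncture, so these can fall under the catch-all if judged related. If classed as expected, they too have no stated route to the form.
- *An event judged unrelated and not on the list:* outside both sentences.

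The article itself makes bleeding foreseeable. The intervention is named for drawing blood, and the Exclusion criteria rule out patients with a clotting disorder.

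**Step 3. Check the acne term.** The trial population has non-allergic rhinopathy, and neither the eligibility criteria, the interventions nor the outcomes involve acne. The term does not belong.

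**Step 4. Illustrate how sensitive an arm of this size is to incomplete capture.** The under-count itself cannot be computed. Assume a true rate p of patients with a given event, and a fraction c of affected patients recorded, independently. Neither is in the article. With n = 25 per arm (Sample size section, before drop-out):

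- expected recorded patients = 25 × p × c
- chance of recording at least one = 1 − (1 − p × c)^25

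| Assumed p | c = 1 | c = 0.5 | c = 0.25 |
|---|---|---|---|
| 5% | 1.25; 0.723 | 0.62; 0.469 | 0.31; 0.270 |
| 10% | 2.5; 0.928 | 1.25; 0.723 | 0.62; 0.469 |
| 20% | 5.0; 0.996 | 2.5; 0.928 | 1.25; 0.723 |
| 30% | 7.5; >0.999 | 3.75; 0.983 | 1.88; 0.858 |

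Each cell gives expected recorded patients, then the chance of at least one. For example, at p = 20% and c = 0.25, p × c = 0.05 and 1 − 0.95^25 = 0.723. If capture were incomplete it would matter in an arm this small. The table is not evidence that capture will be incomplete.

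**The case against.** The strongest reply is that the section should be read as a whole. Adverse events are listed as a safety measure without qualifier, and the monitoring sentence covers pain at other sites and any acupuncture-related event, with no expectedness limit. Since the article treats pricking as a form of acupuncture, expected bleeding or infection can fall within that catch-all. The reporting rule applies to both arms in the same words. No list of expected events is given by which anything would be excluded. The laboratory tests at weeks 0 and 3 do not depend on either judgement.

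Much of this stands, and it rules out several stronger readings.

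- A reader might infer that events count *only* if unexpected and related, so that nasal harms *will* be missed. The monitoring sentence contradicts the first part, and the second does not follow.
- A reader might infer that the list was taken from an acne trial. That is plausible, but the article shows only that the term is out of place.
- A reader might infer that causality is judged unblinded. The practitioner knows the treatment, and the principal investigator has access to the allocation database. The article says who receives the report, not who decides on cause.
- A reader might infer that the experimental arm will look safer and that the arms cannot be compared. The documents do not establish a direction, and the article describes no between-arm safety test.
- The upper bound after no events in 25 patients, 1 − 0.05^(1/25) = 11.3% (one-sided 95%), might be taken as the size of the defect. It assumes full capture and would be the same after the fix.

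What the reply does not remove is the disagreement itself. The monitoring sentence is garbled: it says vital signs are checked by monitoring adverse events. It also does not say that what is found is recorded. Relatedness still limits the catch-all, and the other-sites wording covers pain but not bleeding or infection. Blood counts are insensitive to minor local events. These are faults in what the article prints, not details left to a fuller document.

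**Conclusion.** The point holds as a contradiction in scope together with a wrong term. The sentence that leads to the case report form is narrower than the monitoring sentence, both rest on relatedness, and the list names an acne lesion and no nasal event. Two staff members following the section in good faith could record different events. Foreseeable local events of intranasal pricking, and events judged unrelated, may be under-recorded.

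The size cannot be stated from the documents. The conclusion rests on the wording alone and on no assumed event rate. The primary efficacy analysis is untouched. The repair belongs before recruitment, which the Trial status section says has not begun.

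**What to change.** - **Reconcile the two sentences into one rule.** All adverse events, expected or not and whatever their judged relation to treatment, are recorded on the case report form at each visit in both arms. Expectedness and relatedness are classified afterwards.
- **Correct the list.** Replace the acne term with local events at the treated site, such as bleeding, pain and local infection, asked in the same words in both arms.
- **Protect the blinding.** These questions should be put by someone other than the blinded outcome assessor, or only after outcome assessment is complete. One arm is pricked inside the nostril and the other is needled at LI 20, so answers about nasal bleeding or pain could reveal allocation. Assessor blinding is the only blinding this trial has.

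The cost is revised protocol and case report form wording and slightly more recording. No visit or test is added. How the events are then summarized can be left to the statistical analysis plan.

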#### Sample size

This study is a pilot study to evaluate the clinical effects of pricking blood at ExHN 9 on NAR. Because this trial will be designed for a short duration, lasting 3 weeks, with the intention of decreasing the drop-out rate, the desired sample size for this pilot study is 50 patients, with 25 for each group, assuming a drop-out rate of 20%.

## Discussion

A placebo-control group is a decisive tool to evaluate whether the clinical effectiveness of an intervention is truly due to the characteristic elements of an intervention [19]. Even though several recent large randomized trials found clinically relevant effects of acupuncture over no treatment or routine care, blinded trials comparing acupuncture to sham interventions often reported only minor or no differences [20]. A recent Cochrane review on placebo interventions for all clinical conditions showed that placebo interventions have no important clinical effects in general, but in certain settings, placebo interventions can influence patient-reported outcomes and physical placebos including sham acupuncture were associated with larger effects over no-treatment control groups than pharmacological placebos [21]. Thus, in trials to evaluate the clinical effect of acupuncture treatment, a control group must be included because a sham or placebo control can affect outcomes in certain designed settings. In particular, in Korea, several patients have used acupuncture treatment and are familiar with acupuncture treatment. Because it is difficult to apply a placebo-control, including sham acupuncture, to Korean patients, only minor or no differences are often reported in blinded trials that compare acupuncture to sham interventions [20]. In this study, we will use real acupuncture treatment as the control group. Acupuncture treatment at LI 20 is the most common therapy used to treat patients with nasal disease in the clinical practice of Oriental medicine [9-12]. In this study, the effect of pricking blood at ExHN 9 which is modified acupuncture treatment method, to reduce the nasal congestion and hypersensitivity will be evaluated [13-15]. Therefore, acupuncture treatment at LI 20 will be used as the control group to access the effectiveness of pricking blood at ExHN 9.

The primary goal of treating NAR patients is to give symptomatic relief. So, the primary outcome that will be evaluated in this study is the mean change in TNSS from baseline to the end of the trial. Since NAR is a condition that markedly affects the quality of life, we will also examine the mean change in MiniRQLQ scores from baseline to the end of trial as a secondary outcome.

This study will be the first randomized trial to evaluate the efficacy of pricking blood at ExHN 9 for the treatment of NAR. The main focus of this study is to investigate the effectiveness of pricking blood at ExHN 9 in decreasing the TNSS, as a primary outcome, relative to acupuncture treatment at LI 20, which is commonly used in clinical practice and has been shown to be effective in treating patients with chronic rhinitis including NAR. This trial will provide information needed to answer relevant clinical questions regarding the efficacy of pricking blood at ExHN 9 for the treatment of NAR. Although the size of this trial is small and cannot provide conclusive results on the effectiveness of pricking blood at ExHN 9, if positive results are obtained, a large clinical trial will be conducted in the future.

## Trial status

Not yet recruiting.

## Ethics

The study protocol and the written informed consent were approved by the institutional review board (IRB) of the Oriental Medical Hospital at Kyung Hee Medical Center (KOMC MIRB 2010-04). Each participant will be notified regarding the study protocol. Written informed consent will be obtained from each patient.

## Abbreviations

ALT: Alanine transaminase; AST: Aspartate transaminase; BUN: Blood urea nitrogen; ExHN 9: Neiyingxiang; HRV: Heart rate variation; IRB: Institutional review board; LI 20: Waiyingxiang; LOCF: Last observation carried forward; MAST: Multiple antigen simultaneous test; MCH: Mean cell hemoglobin; MCHC: Mean cell hemoglobin concentration; MCV: Mean cell volume; MiniRQLQ: Mini-rhinoconjunctivitis quality-of-life questionnaire; NAR: Non-allergic rhinopathy; RBC: Red blood cell; RCT: Randomized controlled trial; SD: Standard; WBC: White blood cell.
